## Abstract

Intrusive memories are common following trauma exposure. However, they can develop into a distressing symptom of posttraumatic stress disorder (PTSD). Recent research examining the role of sleep in the development of intrusive memories demonstrates overnight sleep or a daytime nap following analog trauma exposure (ie, a trauma film), compared to a similar period of wake, results in fewer intrusive memories in the following week. This is consistent with research examining participants who have recently experienced trauma, demonstrating sleep disturbances are highly associated with the development of intrusive memories. However, the mechanisms underlying this are not well understood. Identifying those mechanisms is critical to improving interventions to reduce intrusive memories, and thus, the impacts of posttraumatic stress disorder. This study aims to investigate two potential mechanisms underlying the relationship between sleep and intrusive memories; namely, whether sleep-related memory consolidation and/or executive control over spontaneous cognition explains this relationship. These aims will be investigated through an experimental trauma film study in a healthy adult population (*n* = 114), where we will compare the effects of a 2-h nap versus 2-h controlled waking period on intrusive memories for the trauma film. In the subsequent week, we will examine the relationship between sleep the previous night and intrusive memories the following day. The outcomes of this project will provide important insights regarding the mechanism(s) explaining the relationship between sleep and intrusive memory frequency. Findings will provide further direction for research investigating sleep-related effects on intrusive memories and may have implications for intervention post trauma exposure.

Statement of SignificanceSleep following experimental trauma exposure reduces the frequency of intrusive memories. In trauma-exposed populations, sleep is also found to play a role in the development and maintenance of posttraumatic stress disorder symptoms, including intrusive memories. However, there is limited understanding as to how sleep exerts this influence. This study is attempting to fill this gap in the literature by investigating whether memory consolidation for trauma stimuli and/or executive control over spontaneous cognition mediates the relationship between sleep and intrusive memories. Findings from this study will provide insights into sleep’s effect on intrusive memories and may identify new targets for intervention following trauma exposure.

Sleep following experimental trauma exposure reduces the frequency of intrusive memories. In trauma-exposed populations, sleep is also found to play a role in the development and maintenance of posttraumatic stress disorder symptoms, including intrusive memories. However, there is limited understanding as to how sleep exerts this influence. This study is attempting to fill this gap in the literature by investigating whether memory consolidation for trauma stimuli and/or executive control over spontaneous cognition mediates the relationship between sleep and intrusive memories. Findings from this study will provide insights into sleep’s effect on intrusive memories and may identify new targets for intervention following trauma exposure.

## Introduction

Intrusive memories are spontaneous, involuntary intrusions of memories, typically sensory experiences (eg, sights, sounds, smells), into conscious awareness [1–3]. While in many individuals intrusive memories tend to dissipate over time following trauma, for those with posttraumatic stress disorder (PTSD), this symptom can remain distressing and persistent for many years [1]. Sleep disturbance, another common symptom following trauma, is conceptualized as both a symptom of PTSD and a comorbid disorder [4]. Evidence suggests sleep disturbance prior to [5–7] and early after [7–9] trauma predicts the development of PTSD. Sleep disturbance is also related to intrusive memories specifically. For example, sleep disturbance is associated with more frequent intrusive memories in the week after experiencing trauma [10, 11]. Even many years after trauma exposure, disturbed sleep the previous night is still associated with more intrusive memories the following day [12].

Experimentally, the effects of sleep on intrusive memories have been established through the utilization of the trauma film paradigm [13–16]. The trauma film paradigm has been used as an analog of trauma and is a well-established paradigm within the PTSD field, specifically for studying intrusive memories [17]. It is shown to reliably elicit intrusive memories and has been utilized to study a range predictors of intrusive memory development [17], including the role of sleep. In these studies, participants view a distressing film and are allocated to either a sleep or a wake condition following the film. Participants then report on film-related intrusive memories and associated distress over several days [18]. Four separate meta-analyses have each concluded a period of intact sleep following exposure to the analog trauma reduces the number of intrusive memories experienced [19–22]. This has been found in studies examining sleep compared to total overnight sleep deprivation [13], partial sleep deprivation [23], wake during the day [16], or a nap compared to the same period of wake [14, 15]. Several studies also point to a specific role for rapid eye movement (REM) sleep, which, compared to the absence of REM, leads to both fewer intrusions [24, 25] and lower distress associated with intrusions [26]. Overall, both research examining clinical populations and findings of experimental trauma film paradigm studies demonstrate healthy sleep after trauma appears critical for reducing the number of intrusive memories.

However, the mechanism(s) by which sleep reduces intrusive memories remains unknown. Models of intrusive memory development in PTSD propose consolidation of the trauma memory into autobiographical memory networks is one mechanism for reducing intrusive memories [27–29]. This consolidation of the trauma memory is thought to be indicated by enhanced explicit memory, such as an accurate voluntary recall of the trauma memory [16] and improved ability to distinguish between experienced trauma stimuli and similar but new stimuli [13, 30]. As sleep plays an important role in the consolidation of emotional memories [16] and is found to improve voluntary recall of trauma stimuli, yet reduce intrusive memories of trauma stimuli [13], several studies argue the sleep-related reduction in intrusive memories is due to memory consolidation occurring over a period of sleep compared to wake [13, 16, 23, 31].

A second potential mechanism explaining the role of sleep in intrusive memories relates to sleep disturbances increasing disruptive spontaneous cognition (eg, mind wandering), which in turn accounts for the involuntary intrusion of trauma memories into awareness [19, 32]. Mind wandering occurs when, instead of being focused on task relevant demands, attention is captured by internal stream of thought [33]. Notably, increased mind wandering has been observed following both self-reported poor sleep [34] and experimental sleep deprivation [19, 35] and may occur via sleep’s effect on reduced executive control [32]. Therefore, reduced top-down executive control over traumatic autobiographical memories would be expected to increase the likelihood of the memories becoming intrusive. This process may be exacerbated by sleep deprivation, due to the resultant negative impact on executive control [19, 36]. As people frequently experience sleep difficulty following trauma [37], this explanation may represent an important mechanism for the early maintenance of intrusive memories.

In summary, sleep disturbance plays a role in the development of intrusive memories following trauma exposure [19–22]. The critical gap in the literature is understanding the mechanism(s) whereby sleep exerts this influence [36]. The current project will address this through an experimental study in healthy adults. We are utilizing a nap vs wake design, rather than overnight sleep vs sleep deprivation design, as in addition to reducing the frequency of intrusive memories, naps are found to improve memory for a range of emotional [23, 38] and neutral stimuli [39]. Utilizing a nap/wake paradigm also ensures intrusion frequency is due to sleep rather than the effect of total sleep deprivation (eg, if using an overnight wake period) or potential circadian confounds of comparing a day of wake to a night of sleep immediately following exposure to the trauma film. The current study will be the first to examine memory consolidation as a mechanism linking sleep to intrusive memories using a nap versus wake design, as well as the first to examine mind wandering as a mechanism linking sleep to intrusive memories, using any type of design. Additionally, we will examine natural variation in sleep across multiple nights following analog trauma exposure to examine the relationships between sleep the night before and both mind wandering and intrusive memories the following day.

### Aims and hypotheses

The overall objective of this project is to examine two mechanisms underlying the relationship between sleep and the development of involuntary intrusive memories, utilizing a well-established experimental analog trauma exposure. The two mechanisms are:

Improved memory consolidation over periods of sleep leads to integration of the trauma memory into the broader memory network, thereby reducing intrusive memories.Sufficient sleep quality/quantity facilitates executive control over spontaneous cognition, including intrusive memories, decreasing the likelihood of their occurrence.

This study will employ a between-subjects design, with two conditions: (1) 2-h daytime nap opportunity, measured using polysomnography; and (2) equal length of controlled waking. Each condition will include *n* = 57 healthy adults, aged 18–49 years old (total *N* = 114, aiming for equal numbers of women and men). OSF preregistration: https://doi.org/10.17605/OSF.IO/MWAHD

Aim 1: Examine the effect of a daytime nap (vs. wake) on intrusive memory frequency.
Hypothesis 1.We will replicate the established finding that a nap, relative to wake, will result in a reduced number of intrusive memories [14, 15] in the 5 days following viewing the trauma film.

Aim 2: Investigate the effect of sleep-related memory consolidation on intrusive memory frequency.
Hypothesis 2a.A nap, relative to wake, will lead to greater recognition memory for the trauma film stimuli immediately after the nap/wake period, as measured by improved recognition of trauma stimuli from the film and reduced endorsement of lure stimuli (film images never seen).
 Hypothesis 2b.Recognition memory for the trauma film immediately after the nap/wake period will mediate the relationship between sleep condition (nap vs wake) and the number of intrusive memories in the following 5 days.

Aim 3: Investigate the effect of overnight sleep on mind wandering and intrusive memory frequency over a 5-day period following analog trauma exposure.
Hypothesis 3a.Reduced quantity of sleep at night will be associated with increased mind wandering and greater frequency of intrusive memories the next day.
 Hypothesis 3b.Mind wandering will mediate the relationship between sleep the previous night and intrusive memories the following day.

## Methods and Materials

### Study design

There are three phases of participation in the study. Figure 1 outlines the timeline of study participation. During phase 1, 1 week prior to the lab session (days −7 to −1), participants maintain a regular sleep schedule and document adherence with a daily sleep diary and wear actigraphy. On the first day of the study (day −7), participants meet with the researchers to confirm their sleep schedule, learn how to complete a sleep diary, practice a task to be completed during the lab session, and are provided with the actigraphy device.

**Figure 1 f1:**
[figure not shown]
Timeline of study participation. During days −7 to −1, participants maintain a regular sleep schedule. Day 0 (lab session) is indicative of a participant with a habitual wake time of 8 am. Lab session timing depends on participant sleep schedule. All sessions are a maximum of 6 h long. For the night following the lab session, participants follow the regular sleep schedule. For the remaining four nights of sleep, participants sleep ad libitum. During days 1–5, participants complete a daily mind wandering task (sustained attention task), fill out a diary for intrusive memories, and repeat the recognition task on the final day.

Phase 2 is the lab session (day 0). Participants wake up 2 h prior to their habitual wake time. This is to ensure sufficient sleep during the nap and to mildly sleep-deprive the wake group. After reporting to the lab in the morning participants are set-up with polysomnography. Following this, they view an analog trauma film in a dark sound attenuated room. Participants are then randomly assigned to one of the two groups: an experimental (nap) group and a controlled (wake) group, for a 2-h period. During this time, those in the wake group can engage in specific activities provided by the researchers including coloring and puzzles. They are unable to use social media, watch videos, view photos, read, or engage in university study/other work during this time. At the end of this experimental period, polysomnography equipment is removed and there is a 30-min delay period for both groups, to allow for the effects of sleep inertia to subside for the nap group. Participants then complete a recognition memory task for images from the trauma film and a sustained attention task to measure mind wandering (hereinafter referred to as “mind wandering task”) in the same sound attenuated room. Following this, participants are provided with instructions for completing an intrusive memory diary.

Phase 3 includes the remaining 5 days of the experiment. Over the next five nights, we will continue to monitor participant sleep with diaries and actigraphy. Participants complete daily intrusive memory diaries, starting as soon as they leave the lab, with six entries at minimum. During each day, they complete the same mind-wandering task completed during the lab session. The recognition task is repeated on day 5. Following study completion, participants attend a debrief meeting.

### Participants and recruitment

#### Sample size

Our target sample size is 114 participants, with 57 in each condition. This study is powered primarily on Hypothesis 1, the group effect (nap vs. wake) on intrusive memory frequency. Relevant effect sizes were derived from a variety of prior studies, which have also been reported within at least one of four meta-analyses. Previous studies [14, 15, 25] examining the effect of a nap compared to wake on intrusion frequency have detected small to medium effect sizes (Hedges’ *g* = 0.38 [26] and 0.69 [15]) for between-group differences in intrusive memory frequency in the days following the experimental manipulation. Gvozdanovic et al. (2023) [14] also found a nap led to significantly fewer intrusive memories than the wake group, however, an effect size was not provided. For studies examining recognition memory for the trauma film following overnight sleep compared to wake or partial sleep deprivation [13, 23, 40], we calculated a sample size weighted average for Cohen’s *d*, finding a medium effect size of 0.5 for between-group differences where sleep, relative to wake, led to improved recognition memory for the film. Consistent with these studies, to detect a medium effect size of 0.5, with a two-tailed α of 0.05 and 80 per cent power, 57 participants are needed per group (114 participants in total) [41].

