## Analytic strategies

All analyses will be conducted in R.

Aim 1: The effect of a daytime nap (vs wake) on total intrusive memory frequency will be analyzed with a generalized linear mixed-effects model. Sex and day will be included as covariates. A random intercept for participant will be included to account for repeated measures across days.

Aim 2: The effect of sleep-related memory consolidation on intrusive memory frequency will be analyzed with regression and mediation analysis. Specifically, Hypothesis 2a (a nap will lead to greater recognition memory for the trauma film) will be examined with multiple regression, whereby recognition memory immediately after the nap/wake will be predicted by Condition. For Hypothesis 2b (recognition memory will mediate the relationship between sleep and intrusive memories), we will utilize mediation analysis, with Condition as the explanatory variable, recognition memory immediately after the nap/wake as the mediator, and total number of reported intrusive memories as the dependent variable. A Monte Carlo power analysis was conducted for the mediation model. A sample size of *n* = 114 has limited power to detect the indirect effect. Nonetheless, given the strong theoretical rationale for the mediation analysis and the value for future research in determining effect sizes, we will conduct the analysis and consider Hypothesis 2b as a secondary analysis. We will report effect sizes and confidence intervals of each path. We will also conduct parallel exploratory analyses for both Hypotheses 2a and 2b, utilizing recognition memory on day 5, rather than memory immediately following the nap/wake. This will explore the role of longer-delay memory consolidation on intrusive memory. Note, Hypothesis 2b may appear dependent on the success of Aim 1.

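### 57 per group gives about 75% power, not 80%, for the stated effect of 0.5, and that 0.5 is derived from recognition memory, not from the outcome the study is powered on

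*Protocol article*

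**What the plan says.** The Sample size section sets the target: "Our target sample size is 114 participants, with 57 in each condition". It names the outcome that drives the calculation: "This study is powered primarily on Hypothesis 1, the group effect (nap vs. wake) on intrusive memory frequency".

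It then reports two kinds of earlier evidence. For nap versus wake on intrusions it gives Hedges' g values of "0.38 [26] and 0.69 [15]) for between-group differences in intrusive memory frequency", and notes that a third nap study reported no effect size. For recognition memory, from studies of overnight sleep against wake or partial sleep deprivation, it reports a sample-size-weighted average, "finding a medium effect size of 0.5 for between-group differences where sleep, relative to wake, led to improved recognition memory for the film".

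The calculation follows, described as consistent with these studies: "to detect a medium effect size of 0.5", "with a two-tailed α of 0.05 and 80 per cent power", with the result "80 per cent power, 57 participants are needed per group (114 participants in total". The section mentions no dropout allowance, covariate gain, repeated-measures correlation or dispersion.

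Under Analytic strategies, the effect of the nap on intrusions "will be analyzed with a generalized linear mixed-effects model. Sex and day will be included as covariates".

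**The concern.** All the inputs of a standard two-group calculation are printed: effect size, alpha, sidedness, power and equal allocation. The result can therefore be checked directly, and 57 looks too small. The familiar answer for a standardized difference of 0.5 at 80% power is in the low sixties per group.

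There is a second difficulty. The study is said to be powered on intrusive memory frequency after a nap, but the only effect size shown as worked out to 0.5 belongs to another outcome (recognition memory, Hypothesis 2a) and another manipulation (overnight sleep).

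What is at stake is how a null result on Hypothesis 1 would be read. A reader would judge it against a stated 20% risk of missing the planned effect, when the printed inputs imply about 25%. The article itself notes that Hypothesis 2b may appear to depend on Aim 1. Aim 3 concerns overnight sleep in the follow-up days and does not rest on the nap effect.

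**Working it through.** **Inputs**, all from the Sample size section: d = 0.5 on a scale with SD 1; two-tailed alpha 0.05; power 80%; 1:1 allocation; stated result 57 per group.

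**Step 1. Required n, normal approximation.**

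n per group = 2(z₀.₉₇₅ + z₀.₈₀)² / d² = 2(1.960 + 0.842)² / 0.25 = 62.8, so 63.

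**Step 2. Required n, t-test (noncentral t).** 63.77, so 64 per group and 128 in total. The stated 57 is not reproduced. The shortfall is 64 − 57 = 7 per group, or 14 participants.

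**Step 3. Power at 57 per group, d = 0.5.**

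Normal: Φ(0.5·√(57/2) − 1.960) = Φ(2.669 − 1.960) = Φ(0.709) = 76.1%. Noncentral t: 75.4%.

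**Step 4. Effect for which 57 per group gives 80% power.** Noncentral t: d = 0.529.

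**Step 5. Can 57 be reached another way?** All figures are for the t-test at alpha 0.05.

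| Variant | n per group | Agrees with the text? |
|---|---|---|
| d = 0.5, two-sided, 80% | 64 | yes, but it is not 57 |
| d = 0.5, two-sided, 75% | 57 | no, the text says 80% |
| d = 0.53, two-sided, 80% | 57 | no, the text says 0.5 |
| d = 0.5, one-sided, 80% | 51 | no, the text says two-tailed |
| d = 0.5, one-sided, 80%, plus 10% dropout | 57 | no, two-tailed and no dropout stated |
| d = 0.5, two-sided, 90% | 86 | no |

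A rank-based test would need slightly more than the t-test: 64 / 0.955 = 67.0 per group.

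**Step 6. Power at the effects quoted for the outcome of Hypothesis 1**, 57 per group, two-sided t-test.

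| Effect | Power at 57 per group | n per group for 80% |
|---|---|---|
| 0.38 | 52% | 110 |
| 0.50 | 75% | 64 |
| 0.69 | 95% | 34 |

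**The case against.** Four points can be made for the plan.

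- **Rounding.** The 0.5 is a calculated average printed to one decimal. Values from 0.45 to 0.549 would all print as 0.5, and the required n would run from 79 down to 54 per group. An unrounded 0.53 gives 57 exactly, in which case the 80% is right and only the printed effect is imprecise. This is plausible, but it cannot be confirmed from the article, which prints the two g values beside it to two decimals. Even if true, the sentence as printed still needs correcting.
- **The planned test is not a t-test.** Hypothesis 1 uses a generalized linear mixed model on daily data with covariates. A covariate correlation of about 0.3 would bring 63 down to 63 × (1 − 0.3²) = 57.3 per group. But the article offers no such input, frames the calculation as a standardized group difference, and gives nothing on dispersion or zero counts, which could lower power. What stands is that 75.4% is the power of the stated calculation, not a precise figure for the planned model.
- **The source of 0.5.** It lies between the two intrusion effects. Their midpoint, (0.38 + 0.69)/2 = 0.535, would need 56 per group, and the phrase linking the calculation to earlier studies may cover both sets. This stands in part: 0.5 is not contradicted by the intrusion evidence. The text still does not derive it from that evidence.
- **Size.** The gap is under 5 points of power, or 0.03 in detectable effect, and the article is open about limited power for its mediation analyses. That is fair, and it is why a change of wording is enough.

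**Conclusion.** The concern holds. As printed, the effect size, power and sample size cannot all be true: 57 per group gives 75.4% power at d = 0.5, so the risk of missing the planned effect is about 25%, not 20%. Reaching 80% takes 64 per group, or an effect of about 0.53.

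The point about provenance also holds, in a limited form. The study is declared to be powered on intrusions, the derivation shown is for recognition memory, and power at the quoted intrusion effects ranges from 52% to 95%, which the reader is not told.

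These figures assume a two-sample t-test, no covariate gain and 57 analysed per group. The article excludes some participants after the lab session and makes no allowance for it. If 57 is the number enrolled, an assumed loss of 5% to 10% (54 or 51 per group) would lower power at d = 0.5 to about 73% or 71%.

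**What to change.** Keep N = 114 and restate the claim in the Sample size section and in the preregistration, for example:

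> With 57 participants per group and a two-tailed alpha of 0.05, a two-sample t-test has 75% power for d = 0.5 and 80% power for d = 0.53. The value 0.5 is the weighted average from studies of recognition memory after overnight sleep. At the nap effects reported for intrusive memories, power is 52% (g = 0.38) and 95% (g = 0.69).

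If the calculation in fact used an unrounded effect near 0.53, or a covariate or repeated-measures gain, print that input instead and show that it yields 57.

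The cost is wording only, with no extra participants and no change to design or analysis. The stated power becomes less favourable. Keeping the 80% claim at d = 0.5 would instead require 128 participants, 14 more than planned.
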